## Abstract

**Background:**

Radiofrequency ablation (RFA) and microwave ablation (MWA) are widely accepted techniques to eliminate small unresectable colorectal liver metastases (CRLM). Although previous studies labelled thermal ablation inferior to surgical resection, the apparent selection bias when comparing patients with unresectable disease to surgical candidates, the superior safety profile, and the competitive overall survival results for the more recent reports mandate the setup of a randomized controlled trial. The objective of the COLLISION trial is to prove non-inferiority of thermal ablation compared to hepatic resection in patients with at least one resectable and ablatable CRLM and no extrahepatic disease.

**Methods:**

In this two-arm, single-blind multi-center phase-III clinical trial, six hundred and eighteen patients with at least one CRLM (≤3 cm) will be included to undergo either surgical resection or thermal ablation of appointed target lesion(s) (≤3 cm). Primary endpoint is OS (overall survival, intention-to-treat analysis). Main secondary endpoints are overall disease-free survival (DFS), time to progression (TTP), time to local progression (TTLP), primary and assisted technique efficacy (PTE, ATE), procedural morbidity and mortality, length of hospital stay, assessment of pain and quality of life (QoL), cost-effectiveness ratio (ICER) and quality-adjusted life years (QALY).

**Discussion:**

If thermal ablation proves to be non-inferior in treating lesions ≤3 cm, a switch in treatment-method may lead to a reduction of the post-procedural morbidity and mortality, length of hospital stay and incremental costs without compromising oncological outcome for patients with CRLM.

**Trial registration:**

NCT03088150, January 11th 2017.

## Background

Colorectal cancer is the third most common malignancy worldwide and the second most common cause of cancer related death in developed countries [1, 2]. Approximately half of the patients will develop colorectal liver metastases (CRLM). Only 10–15% are considered eligible for partial hepatectomy (PH), due to (1) an impaired general health status, (2) a history of extensive abdominal surgery, (3) the presence of lesions with an unfavourable anatomical location or (4) an insufficient future liver remnant to resect all lesions [3–7]. These patients are usually treated with chemotherapy and/or thermal ablation, alone or in combination with PH.

Contradictory to most cancer types, long-term survival and even cure is possible in a subset of patients with CRLM [8]. Median overall survival (OS) of untreated CRLM (receiving only symptomatic therapy) is 4.5–12 months [9]. Chemotherapy has improved OS, but OS remains humble at 15–20 months [10, 11].

Surgical resection of the metastases has long been considered the only curative treatment option. In the past few years, radiofrequency ablation (RFA) and microwave ablation (MWA) techniques have rapidly worked their way into clinical guidelines for treatment of unresectable liver tumours [12]. For solitary small (< 2 cm) hepatocellular carcinomas, international guidelines have shifted from surgery to minimally-invasive percutaneous thermal ablation because local control rates have reached 100% [6, 13–17].

Four recent series reported a comparable OS for thermal ablation versus surgical resection [14, 18–20]. These results have led to the discussion whether or not thermal ablation – being less invasive – should be favoured over resection for smaller lesions. Despite this, 5-year OS (25–55%) of thermal ablation for patients with unresectable CRLM has been labelled inferior to surgical resection for patients with resectable CRLM according to previous meta-analyses and systematic reviews [21–29]. These results should be interpreted with caution due to the apparent selection bias. At this point, there are no high-quality randomized controlled trials comparing thermal ablation to surgical resection for resectable CRLM, even though the need has previously been suggested by various authors [8, 30, 31]. To prove non-inferiority, we have designed a two-arm single-blind multi-center phase-III randomized controlled trial comparing surgical resection (standard of care) to thermal ablation (experimental arm) for resectable and ablatable CRLM ≤3 cm.

## Design/methods

### Design

COLLISION is a national, single-blind, multi-center, phase-III trial that is organized by the Amsterdam University Medical Centres (location VUmc) in Amsterdam, the Netherlands. The study is accommodated by the Dutch Colorectal Cancer Group (DCCG) and formally endorsed by the Dutch national covering patient federations, Dutch national societies for interventional radiology (NVIR), radiology (NVvR), surgery (NVvH), and the liver surgery working group (WLC).). Patients will be recruited in, at least sixteen, high-volume centres for liver surgery throughout the Netherlands: Amsterdam UMC (location VUmc), Amsterdam; Amsterdam UMC (location AMC), Amsterdam; Leiden University Medical Center (LUMC), Leiden; Radboud University Medical Center, Nijmegen; Maastricht University Medical Center (MUMC), Maastricht; Antoni van Leeuwenhoek (AvL), Amsterdam; Medical Center Leeuwarden (MCL), Leeuwarden; Ziekenhuis Gelderse Vallei (ZGV), Ede; Isala Klinieken, Zwolle; Deventer Ziekenhuis, Deventer; Westfriesgasthuis, Hoorn; Erasmus Medical Center (EMC), Rotterdam; Jeroen Bosch Ziekenhuis (JBZ), Den Bosch; Medisch Spectrum Twente (MST), Enschede; Onze Lieve Vrouwe Gasthuis (OLVG), Amsterdam; University Medical Center (UMCU), Utrecht). The protocol has been approved by the Medical Ethical Review Board (METc) of the Amsterdam University Medical Centres (location VUmc) for Dutch national approval (no. 2016.561). The trial is investigator-sponsored by Medtronic PLC, independent of industry and registered at clinicaltrials.gov (*NCT03088150*, January 11th 2017). The trial will be conducted in accordance with the Declaration of Helsinki (64th version, October 2013) and the guidelines for Good Clinical Practice (GCP). The in- and exclusion criteria are summarized in Table 1.

**Table 1 Tab1:** In- and exclusion criteria

Inclusion criteria	Exclusion criteria
Histological documentation of primary colorectal tumour	No target lesions suitable for both resection and ablation
Age > 18 years	Radical treatment unfeasible or unsafe (e.g. insufficient future liver remnant [FLR])
At least one CRLM size ≤3 cm eligible for both surgical resection and thermal ablation (target lesions)	Any surgical resection or focal ablative liver therapy for CRLM prior to inclusion
Additional unresectable CRLM should be ≤3 cm and ablatable	The presence of extrahepatic nodal or non-nodal metastases
Additional unablatable CRLM should be resectable	Immunotherapy ≤6 weeks prior to the procedure
Maximum number of CRLM 10	Chemotherapy ≤6 weeks prior to the procedure
Resection for resectable lesions considered possible obtaining negative resection margins (R0) and preserving adequate liver reserve	Pregnant or breast-feeding subjects. Women of childbearing potential must have a negative pregnancy test performed within 7 days of the start of treatment
Resectability and ablatability should be re-confirmed by intra-operative ultrasound (IOUS) and full surgical exploration	Compromised liver function (e.g. signs of portal hypertension, INR > 1,5 without use of anticoagulants, ascites)
Eastern Cooperative Oncology Group status (ECOG) 0–2	Uncontrolled infections (> grade 2 NCI-CTC version 3.0)
American Society of Anesthesiologists (ASA) grade 1–3	Severe allergy to contrast media not controlled with premedication
Life expectancy of at least 12 weeks	Any condition that is unstable or that could jeopardize the safety of the subject and their compliance in the study;
Adequate bone marrow, liver, and renal function as assessed by local usual laboratory tests. As usual, these results should be judged by the local investigator and should be conducted within 7 days prior to definite inclusion. Written informed consent	Substance abuse, medical, psychological or social conditions

The total duration of the study is around 13 years considering an inclusion time of 3 years and a minimum follow-up period of 10 years. All participants will provide written informed consent.The flow diagram of is shown in Fig. 1.

**Fig. 1 Fig1:**
[figure not shown]
Flow diagram of study procedure

#### Start COLLISION trial

Inclusion, randomization and treatments started in two hospitals by the end of 2017. Due to formal approval procedures by local authorities, only AmsterdamUMC (location VUmc) and ZGV Ede were able to include patients from the beginning. From May 2018, RadboudUMC, LUMC, MCL, Isala Klinieken and Westfries Gasthuis were also able to participate. Numerous other Dutch high-volume liver centres, which are mentioned above, are waiting for local approval and will participate in the near future.

#### Eligibility

Potential candidates will be registered and undergo routine pre-procedural work-up: baseline full blood examination, carcinoembryonic antigen (CEA), bone marrow, liver, and renal function -, anaesthetic review, ceCT of the chest and abdomen and either an upper abdominal ceMRI or a total body ^18^F-FDG PET-CT using upper abdominal ceMRI as problem solver. Patients with ≥1 resectable and ablatable CRLM (≤3 cm), no extrahepatic disease and a good performance status (WHO 0–2) are considered eligible. Supplementary resections for resectable lesions > 3 cm and thermal ablations for unresectable CRLM ≤3 cm are allowed with a maximum number of CRLM of 10 (Table 1).

Eligible patients will be stratified into low-, intermediate- and high disease burden after assessment by an expert panel (Fig. 1). The panel, consisting of at least two diagnostic radiologists, two interventional radiologists and two hepatobiliary and/or oncological surgeons, will appoint lesions that are resectable and ablatable as target lesions, resectable and unablatable lesions as unablatable lesions and ablatable but unresectable lesions as unresectable lesions. All unablatable lesions should be resectable and all unresectable lesions should be ≤3 cm and ablatable. Because definitions of resectability and ablatability can vary dramatically from one center to the other and from one specialist to the other, the panel has to agree with the treating physicians’ treatment plan. If the panel disagrees, the panel and the treating physicians must reach consensus before the patient can be enrolled.

### Methods

Participating centres should have extensive experience in the field of both hepatic surgery and thermal liver tumour ablation, defined as performing ≥20 procedures annually. Treating surgeons and interventional radiologists should be board certified and have performed and/or supervised ≥100 procedures.

#### Inclusion

After having obtained written informed consent by the outpatient clinic doctor, patients will be formally included. The patient should be scheduled to undergo the procedure within a time-frame of maximum 6 weeks hereafter. Patients suitable for either laparoscopic resection or percutaneous ablation (Subgroup A, low disease burden; 1–3 target lesions) will be randomized prior to the procedure. All other patients will undergo open laparotomy with surgical inspection of the abdominal cavity and intra-operative ultrasound (IOUS).

#### Exclusion (drop-outs)

Despite improvements in preoperative imaging technology, the intraoperative use of ultrasonography remains of crucial importance [32]. The detection rate of preoperatively unknown lesions is still high (up to 50%) with considerable consequences on treatment strategy [32]. Following surgical inspection and IOUS the inclusion criteria need to be reconfirmed prior to randomization. If (1) a radical procedure is no longer considered safe or feasible, if (2) > 10 CRLM are present, if (3) extrahepatic disease is detected, or if (4) no lesion can be appointed as target lesion, the patient cannot be included in the study and will be treated as non-study object. Additional CRLM suitable for both resection and ablation ≤3 cm will be appointed as new target lesions. Additional unresectable lesions ≤3 cm that are suitable for thermal ablation should be ablated if possible and vice versa additionally detected unablatable lesions should be resected. Lesions, preprocedurally appointed as target lesions, that prove unsuitable for one treatment modality based on IOUS lose their status and should be treated with the alternate modality (lesion shifts from target lesion to unablatable or unresectable lesion).

#### Laparotomy

The surgical explorative procedure of participants in this study is identical to standard procedures for non-study objects. A right subcostal incision is performed. The abdominal cavity will be explored in order to exclude extrahepatic tumour manifestations. An IOUS to exclude additional CRLM and for final confirmation of resectability will always be performed.

#### Randomization

Patients with limited disease burden (max. 3 lesions ≤3 cm) that are suitable for percutaneous ablation or laparoscopic resection will be randomized, prior to the procedure, into one of two arms, arm A and arm B. All other patients will undergo laparotomy with IOUS and surgical inspection and will, if still considered eligible, be randomized during general anaesthesia. Patients included in study arm A will undergo resection of hepatic metastases, allowing thermal ablation for additional unresectable lesions. Patients included in study arm B will undergo ultrasound guided thermal ablation of hepatic metastases, allowing resection for additional unablatable lesions (Fig. 1).

Randomization is centralized and performed through a web-based module (Castor EDC®) [33], which is accessible 7 days a week, 24 h per day]. For open procedures randomization will be performed shortly after surgical inspection and IOUS with the patient under general anaesthesia. Both the experimenter(s) and the participant will be unaware of the eventual treatment arm prior to the procedure; after the procedure the patient will remain unaware (single-blind).Because follow-up imaging will reveal the nature of the focal therapy and because knowledge about the actual procedure and pathological confirmation of tumour free margins is required to reliably assess ^18^F-FDG PET-CT follow-up scans, the panel’s diagnostic abdominal radiologists and nuclear physicians need to be informed about the specific treatment history.

Changes in insights detected after randomization do not allow patient’s exclusion. These patients will remain in their originally appointed group according to the intention-to-treat analysis. For example, if, after being randomized into the resection arm, a target lesion proves unresectable during surgical tissue preparation and dissection, the patient will remain in arm A (resection) even if the lesion was eventually ablated or left untreated.

#### Surgical resection

In case of randomization to surgical resection, the surgeon will remove all target lesions as well as all additional unablatable lesions. The extent of the resection, the resection margins and the specific technique is at the discretion of the performing liver surgeon. Complications encountered during the procedure will be noted. Postoperative care will be on the recovery and subsequently on either the surgery ward or medium care whenever deemed necessary. General ‘resectability’ criteria are shown in Table 2.

**Table 2 Tab2:** General ‘resectability’ and ‘ablatability’ criteria

General ‘resectability criteria’	General ‘ablatability criteria’
No size limit	Maximum CRLM size ≤3 cm
Aiming at negative (R0) margins	Aiming at a tumour free margin of > 10 mm
Leave sufficient FLR (> 20% normal functioning liver parenchyma; > 30% post-chemotherapy)	Leave sufficient FLR (> 20% normal functioning liver parenchyma; > 30% post-chemotherapy)
Portal vein embolization of the (most) affected liver lobe may be considered for patients with insufficient FLR	To preserve the major bile ducts (common, right and left hepatic duct) a minimum distance (lesion to major bile duct) of 15 mm is required
At least one of three hepatic veins should be preserved and both the portal venous and hepatic arterial blood flow in the future liver remnant should be remain unharmed	Radical ablation(s) with or without surgical resections for additional unablatable lesions
Approachable surgical field, without extensive scar formation, major surgical adhesions and/or intestinal herniations (risk of major morbidity estimated > 20%; risk of mortality estimated > 5%)	To avoid collateral damage to the intestines a minimum distance to the stomach, small bowel and colon of 15 mm should be pursued in open procedures and respected in percutaneous procedures; Pneumo- or hydrodissections to shift bowels are allowed
Maximum total number of CRLM 10	Maximum total number of CRLM 10

#### Thermal ablation

The safety, feasibility and preferred type of thermal ablation(s) is at the discretion of the interventional radiologist. Ablations are performed according to the CIRSE quality improvement guidelines with an intentional tumour free ablation margin of at least 1 cm [34].

Patients with limited disease burden (max. 3 lesions ≤3 cm) and no contra-indications for a percutaneous approach will be randomized prior to the procedure. Contra-indications for a percutaneous approach are proximity of critical structures. To avoid collateral damage to intestines a minimum distance to the stomach, small bowel and colon of 15 mm should be respected. Laparoscopic approach is allowed. Pneumo- and hydrodissections are allowed. Pringle-manoeuvres are not allowed.

Following percutaneous ablations, a ceCT or ceMRI should always be performed for ablated lesions > 2 cm and for lesions 0–2 cm with radiologically unclear margins after the ablation. Unequivocal local site residues or insufficient tumour-free margins should be re-ablated (completion ablation) within 4 weeks after the initial ablation. If re-ablated within 4 weeks, the residue/insufficient margins count as technically unsuccessful ablations, but not as a tumour recurring event when assessing the primary technique efficacy, local progression-free and disease-free survival. Patients with limited disease burden plus a contra-indication for both percutaneous ablation and for laparoscopic surgery and patients with intermediate or high disease burden will be randomized during open laparotomy.

The probes are connected to compatible and commercially available generators. Ablations will be performed according to the protocols provided by the manufacturers. If necessary, the needle electrodes will be repositioned for one or more overlapping ablations. The proximity of a large portal or systemic vein or hepatic artery is no contraindication for performing the thermal ablation.

The definition of a technically successful ablation is based upon the specific protocols established by the device manufacturers in combination with an immediate post-procedurally performed US (fully hyperechoic ablation zone with an intentional margin of at least 1 cm) [7]. Necessity for re-ablations and/or needle repositioning will be judged by the performing interventional radiologist. Postoperative care will be on the recovery room and subsequently on either the surgery ward or medium care whenever deemed necessary. A quality-control ceCT can be performed within 1–6 weeks after the initial treatment to assess for a completion-procedure [7]. General ‘ablatability’ criteria are shown in Table 2.

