#### Follow-up

Conferring to national guidelines follow-up will include imaging, laboratory tests including tumour markers (CEA) and clinical examination every 3 months for the first year and every 6 months hereafter. Follow-up cross-sectional imaging should include at least an abdominal ceCT or upper abdominal ceMRI at the given time-points. Participating centres are free to add ^18^F-FDG PET-CTs at specific time-points or to use alternating specific modalities, as long as the follow-up protocol is pre-approved by the trial coordinators and as long as follow-up imaging is identical for both treatment arms. Quality of life questionnaires will be assessed at baseline, every 3 months for the first year and every 6 months hereafter accordingly. Data will be collected in Castor EDC® [33], only available for related research investigators.

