## Discussion

The recently published primary efficacy rates (complete ablation after the first procedure) of RFA and MWA for small CRLM have approached the reported resection plane recurrence rates for similar sized lesions [6]^,^ [14–17], [21]. Hence the issue of ablation site recurrences, that has previously prevented its widespread adoption, may be outdated. The relative ease to percutaneously re-ablate potential site recurrences, nowadays in the setting of a one-day admission under conscious sedation, has further downgraded its relevance.

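### Residue or a short margin re-ablated within 4 weeks is not a recurrence event, a rule stated for ablation with no counterpart for resection, so any shift in PTE, local progression-free survival and DFS favours arm B

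*Protocol article*

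**What the plan says.** The Thermal ablation section tells centres what to do with incomplete treatment: "Unequivocal local site residues or insufficient tumour-free margins should be re-ablated (completion ablation) within 4 weeks after the initial ablation". It then fixes how a site treated again in that time is scored: "the residue/insufficient margins count as technically unsuccessful ablations, but not as a tumour recurring event when assessing the primary technique efficacy". The rule also covers DFS and local progression-free survival.

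Two early imaging steps appear in the same section. One is required in some cases: "Following percutaneous ablations, a ceCT or ceMRI should always be performed for ablated lesions > 2 cm", and also for smaller lesions whose margins are unclear. The other is optional: "A quality-control ceCT can be performed within 1–6 weeks after the initial treatment to assess for a completion-procedure".

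The Surgical resection section gives no early scan, no completion window and no scoring rule for residual disease. The Follow-up section schedules imaging every 3 months in the first year for everyone. The Statistical methods section bases PTE on recurrence of target lesions after the initial local treatment, and ATE on recurrence after additional local treatments, with at least 12 months of follow-up.

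**The concern.** The scoring rule removes a class of early failures from three comparative endpoints, and it is written for one technique. Local control is where the article itself reports ablation as weaker: its section comparing partial hepatectomy with thermal ablation cites RFA as inferior to resection on local progression-free survival and DFS. If early failures are looked for and then excused mainly in arm B, part of any apparent equality in local control could come from the counting rule. The performing interventional radiologist, who is not blinded, judges whether re-ablation is needed, so the same decision settles whether an event exists.

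The 4-week limit adds a second problem. The scan that may trigger a completion procedure can be made after that limit has passed.

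**Working it through.** **The plan's own design figure.** The only computed figure is the overall-survival sample size. Inputs from the sample size section: one-sided alpha 0.05, power 0.80, margin HR 1.3, true HR 1.0, 1:1 allocation, event probability 0.6.

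- Events = 4 × (1.645 + 0.842)² / (ln 1.3)² = 359.3.
- Patients = 359.3 / 0.6 = 598.8, rounded up to 599.
- 599 / 0.97 gives 618 randomized, and 618 / 0.90 gives 687 included.

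This reproduces the plan. None of its inputs depends on the exemption.

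**The two arms side by side.**

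| Step | After ablation | After resection |
|---|---|---|
| Early imaging for residue | Required after some percutaneous ablations; otherwise optional at 1–6 weeks | None stated |
| First scheduled follow-up scan | About 3 months | About 3 months |
| Early retreated residue | Exempt if re-ablated by 4 weeks | No rule stated |

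Ablation can occur in arm A, for additional unresectable lesions or for a target lesion that proves unresectable after randomization. The exemption could therefore apply there, but for PTE, which concerns target lesions, it falls almost wholly on arm B. Residue after resection would first be looked for at about 3 months, where no exemption is written.

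**The two windows.** Take one residue. Re-ablated in week 3, it is exempt. Found on the optional scan in week 5 and re-ablated then, it lies outside the exemption and by implication counts. The lesion is the same; only the date of re-ablation differs.

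**Direction, by illustration only.** Assume the same true per-patient local failure L in both arms, a share f of arm B failures re-ablated by 4 weeks and controlled afterwards, and none exempted in arm A. The observed arm B rate is L(1 − f), and the apparent HR is ln(1 − L(1 − f)) / ln(1 − L). L and f are assumptions. The middle value of L is the article's RFA local recurrence figure, 9/56 = 16.1%.

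| L | f | Observed in B | Gap, points | Apparent HR |
|---|---|---|---|---|
| 5% | 10% | 4.5% | 0.5 | 0.90 |
| 5% | 50% | 2.5% | 2.5 | 0.49 |
| 16.1% | 10% | 14.5% | 1.6 | 0.89 |
| 16.1% | 25% | 12.1% | 4.0 | 0.73 |
| 16.1% | 50% | 8.05% | 8.05 | 0.48 |
| 20% | 10% | 18% | 2 | 0.89 |
| 20% | 50% | 10% | 10 | 0.47 |

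The apparent HR is roughly 1 − f, so everything depends on a share that the article does not give.

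**DFS.** Assume an arm B event proportion p of 0.6 to 0.8 under the exemption, and a share c of 2% to 10% of arm B patients exempted who later have events like the others. Counting them gives c + (1 − c)p. The ratio of hazards, exempt to strict, is ln(1 − p) / [ln(1 − p) + ln(1 − c)]. It runs from 0.988 (p = 0.8, c = 0.02) to 0.897 (p = 0.6, c = 0.10), a reduction of about 1% to 10%. The effect is diluted because DFS events are mostly other events.

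**The case against.** The strongest defence is that an early completion ablation is part of the initial treatment. The trial's PTE rests on recurrence, and technical success is a separate concept, so an ablation can be technically unsuccessful without being a recurrence. The rule is stated openly, these cases stay on record as technical failures, and a later recurrence at the site is not exempted. The article is condensed, and the full protocol may hold a rule for arm A. All of this is fair. It makes the exemption defensible in principle, but it does not supply a parallel rule for resection or remove the mismatch between 4 and 6 weeks.

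Four stronger readings are tempting and are not supported.

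- **That the early scans breach the rule on equal imaging.** The condition "as long as follow-up imaging is identical for both treatment arms" concerns scheduled follow-up. The early scans are post-procedural quality control.
- **That the exemption contradicts the trial's PTE definition.** The Discussion's phrase "primary efficacy rates (complete ablation after the first procedure" describes published rates. The trial's own definition is in Statistical methods.
- **That every short ablation margin should be a PTE failure in the main analysis.** Nothing makes a narrow or positive resection margin an event in arm A, so this would tilt the comparison against arm B.
- **That a given fraction of local failures is hidden.** Setting an assumed per-lesion re-ablation rate against 16.1% mixes lesions with patients. That 16.1% comes from patients given chemotherapy plus RFA for unresectable disease, and the article does not say whether residue corrected early is included.

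**Conclusion.** The point holds for secondary endpoints only. As written, the exemption can remove events almost solely in arm B, where early imaging also looks for them, and the article states no equivalent for resection. Any shift in PTE, local progression-free survival or DFS therefore favours arm B. This assumes that residual disease after resection counts when it is found at scheduled follow-up; a parallel rule in the full protocol would narrow the gap. The document states no penalty on surgery; the defect is the missing counterpart.

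The size cannot be computed from the document. Under the assumptions shown, the shift could matter for local control and is probably small for DFS. Overall survival and its sample size are unaffected. Separately, the 4-week and 1–6-week statements allow identical residue to be scored differently by date of re-ablation.

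**What to change.** 1. State one event rule for residual disease that is retreated early, and apply it to both arms for PTE, local progression and DFS.
2. Prespecify a sensitivity analysis in which residue retreated within the window counts as an event on its detection date in either arm. For PTE it counts as a first-procedure failure, with the retreatment credited to ATE. Because early imaging is described only after ablation, this analysis may lean against arm B, so it should be read beside the main analysis and not replace it.
3. Report the number of completion procedures per arm, so that readers can see how much depends on the rule.
4. Reconcile the 4-week limit with the 1–6-week scan. Which timing is appropriate is for the investigators to settle; the scoring rule should then follow it.

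The cost is some endpoint wording, one extra analysis and one tabulated count. Arm B local-control results will look slightly less favourable in the sensitivity analysis. Sample size and the primary analysis do not change.

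### The exemption for residue re-treated within 4 weeks is written for ablation only, so PTE, local progression and DFS can lean towards the ablation arm

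*Protocol article*

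**What the plan says.** All references are to the protocol article.

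- **Thermal ablation, imaging.** "Following percutaneous ablations, a ceCT or ceMRI should always be performed for ablated lesions > 2 cm", and also for smaller lesions whose margins are unclear. Unequivocal residue or an insufficient margin "should be re-ablated (completion ablation) within 4 weeks after the initial ablation".
- **Thermal ablation, scoring.** Findings of this kind that are re-treated inside that window "count as technically unsuccessful ablations, but not as a tumour recurring event when assessing the primary technique efficacy, local progression-free and disease-free survival".
- **Thermal ablation, optional scan.** "A quality-control ceCT can be performed within 1–6 weeks after the initial treatment to assess for a completion-procedure".
- **Surgical resection.** "The extent of the resection, the resection margins and the specific technique is at the discretion of the performing liver surgeon". The section states no early scan, no completion window and no exemption from events.
- **Follow-up.** The first routine imaging is at 3 months, and the follow-up imaging must be the same in both arms.
- **Statistical methods.** PTE is built on recurrence of target lesions following the *initial local treatment*. Assisted technique efficacy (ATE) is built on recurrence following additional local treatments.
- **Primary and secondary objectives.** The primary endpoint is overall survival. PTE, ATE, DFS and time to local progression are main secondary endpoints.

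**The concern.** This is an explicit scoring rule, not a detail left for an analysis plan, and it is attached to one treatment. Take a target lesion that is not fully eliminated at the first procedure. If it was ablated, an early scan may show the residue, a second session may follow within 4 weeks, and no event is scored for PTE, local progression-free survival or DFS. If it was resected, no early scan is stated, the residue would surface at 3 months, and nothing exempts it. The same kind of first-procedure failure can thus be scored differently by arm, in favour of the experimental arm.

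Local control is where ablation has been doubted. The article's own Discussion says that ablation-site recurrence previously held back adoption. A scoring advantage on exactly these endpoints would weaken the supporting evidence, even though the primary endpoint does not depend on it.

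**Working it through.** **1. What is not affected.** Inputs from Sample size calculation and statistical considerations: margin HR 1.3, one-sided alpha 0.05, power 0.80, 1:1 allocation, event probability 0.6.

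- Events = 4 × (1.645 + 0.842)² / (ln 1.3)² = 359.3
- Patients = 359.3 / 0.6 = 598.8, so 599
- Randomized = 599 / 0.97, so 618; included = 618 / 0.90, so 687

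The plan's figures reproduce. They concern overall survival only, so the exemption does not touch them.

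**2. The rule by arm, for a target lesion with residue after the first procedure.**

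| | Ablated target lesion | Resected target lesion |
|---|---|---|
| Early scan stated | Yes after percutaneous ablation (over 2 cm, or unclear margins); optional at 1–6 weeks | None |
| Re-treatment window stated | 4 weeks | None |
| Recorded as technical failure | Yes | Not stated |
| Event for PTE, local progression-free survival, DFS | No, if re-ablated in the window | No exemption stated |

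**3. Fit with the PTE definition.** Statistical methods separates the initial local treatment from additional ones. Thermal ablation does not say on which side a completion ablation falls. The two sections agree only if it is part of the initial treatment, and that is nowhere stated.

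**4. Internal timing.** The optional scan may be as late as week 6, but the exemption ends at week 4. Residue found in week 5 or 6 falls outside it, so event status depends partly on when an optional scan was booked. The two statements must be reconciled for scoring purposes.

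**5. Illustration of size (assumed inputs).** The article gives no completion-ablation rate. Let p be the first-procedure local failure, equal in both arms, and s the share of ablation failures that are re-ablated in the window and stay controlled. The ablation arm then scores q = p(1 − s), and the artificial gain is d = p × s. Take p = 9/56 = 16.1%, borrowed from the Radiofrequency ablation section. That figure is local site recurrence in patients with unresectable disease, so it is only a stand-in.

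Chance of two-sided p < 0.05 with 309 per arm = Φ((d − 1.96 × SE0)/SE1), with SE0 pooled and SE1 unpooled:

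| s | q | d | SE0 | SE1 | Chance of p < 0.05 |
|---|---|---|---|---|---|
| 10% | 14.5% | 1.6 points | 0.0289 | 0.0289 | 8% |
| 25% | 12.1% | 4.0 points | 0.0280 | 0.0279 | 30% |
| 50% | 8.0% | 8.0 points | 0.0262 | 0.0260 | 87% |

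For scale, the 95% half-width of a PTE difference at 10% failure is 1.96 × √(2 × 0.1 × 0.9 / 309) = 0.047, or 4.7 points. Both calculations treat 309 patients as 309 independent lesions, although patients may have several target lesions.

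**The case against.** The other side has several good points.

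- **Nothing is hidden.** A reader might infer that first-pass failures disappear. They do not: the same sentence records them as technically unsuccessful ablations, and nothing exempts a later recurrence of the re-ablated lesion. This stands.
- **The Discussion does not define the endpoint.** A reader might see a contradiction with "primary efficacy rates (complete ablation after the first procedure". That phrase describes published rates, not this trial's PTE. This stands. The wording to reconcile is in Statistical methods.
- **Margins are not clearly asymmetric.** A reader might infer that an insufficient margin is forgiven after ablation and penalised after resection. No text makes a positive resection margin an event. The asymmetry is clear only for residue.
- **The exemption may offset extra imaging.** Without it, an early scan in one arm could produce events that the other arm cannot yet show. This is a fair reason to have an exemption, but not to word it for one treatment only. It also limits how a sensitivity analysis without the exemption can be read.
- **Reach is limited.** The mandatory early scan follows percutaneous ablation only. Additional unresectable lesions ablated in the resection arm could also use the rule for DFS. The full protocol, which is not shown, may contain a rule for resection.

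These points narrow the concern to residue at target lesions and to secondary endpoints. They do not remove it, because the article fixes the exemption in the ablation section alone.

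**Conclusion.** The point holds for secondary endpoints. As written, residue re-treated within 4 weeks is exempt as an event after ablation, and no equivalent is stated for resected target lesions. PTE, local progression and DFS can therefore favour ablation by an amount that the documents do not allow to be estimated. The 1.6 to 8.0 points above rest on an equal, borrowed failure rate, an assumed exempted share and no exemption at all in the resection arm. The upper end needs half of all ablation failures to be re-ablated in time and to stay controlled.

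Two stronger conclusions are tempting and unsupported. One is that PTE is raised by 5 to 15 points: this follows only if 5–15% of ablated target lesions are re-ablated in the window, a rate with no basis in the article. The other is that every completion ablation should be scored as a PTE failure. That would fail lesions re-ablated only for a narrow margin while a positive resection margin remains a success, which creates a new asymmetry.

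Overall survival, the non-inferiority conclusion on it, and the sample size are not affected.

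**What to change.** 1. In Statistical methods and Thermal ablation, state whether a completion procedure belongs to the initial local treatment, so that PTE and ATE can be told apart.
2. State one event rule for residue at a target lesion re-treated within the same window, and apply it to both arms for PTE, local progression and DFS. Name the endpoints as in the objectives: the exemption refers to local progression-free survival, while the listed endpoint is time to local progression.
3. Report the number and rate of completion procedures per arm beside PTE.
4. Add a sensitivity analysis that counts unequivocal residue re-treated within 4 weeks as an event, but not lesions re-ablated only for a narrow margin.

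The cost is definition wording and slightly more analysis work, with no change to patient care or sample size. The ablation arm may look slightly less favourable in the sensitivity analysis. That analysis also carries the earlier imaging in that arm and should be read with this in mind.
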